**Fig. 1 Fig1:**
[figure not shown]
Conceptual modelling of the relationships between the parenting and the outcomes of healthy lifestyle in children

Connectedness to nature/ relatedness is a relatively new concept that, to date, has been investigated primarily in adults [28]. The concept suggests, for example, that engaging in activities in a natural environment can induce a feeling of Connectedness to nature. Exposing preschool children to nature and to thinking about nature in different ways could stimulate Nature Relatedness [29, 30] as a measurable construct. When children are placed in a natural setting, they tend to engage more in active play [15, 17, 18]. As noted above, parents are children’s role models [12], and we therefore believe that connecting parents and other caregivers (particular situation in Hong Kong, which includes grandparents and domestic helpers) with nature will have benefits for their children [12]. Many habits and attitudes are developed early in life, and those related to the natural world are no exception. In fact, children are inherently interested in their environment and in nature in general [21, 31]. We hypothesise that both indoor and outdoor nature-related activities may induce Connectedness to nature and bring about positive changes in both eating and activity habits (short-term outcomes) in preschool children, in turn leading to a healthier lifestyle (long-term outcomes) (Fig. 1).

### The pilot programme Play & Grow

Play & Grow is a 10-week family-based, multi-component healthy lifestyle programme for families with preschool children aged 2 to 4, and was developed and tested in a pilot study (*n* = 39, aged 2.15, SD = .88, retention rate of 93 %) by the PI and her team. The aim of Play & Grow is to encourage healthy eating habits and active play in children from an early age, and to bring about healthy behavioural changes in families. The programme also includes a Connectedness to nature element designed to equip parents with environmental knowledge and skills. The generated pre- and post-test comparison data indicated the effectiveness of the programme (not presented here). A detailed manual and full resource kit were created, and each session consisted of: (i) a 15-min theoretical education component (food, activity, Connectedness to nature), and (ii) a 30-min component on indoor and outdoor nature-related activities, such as playing with objects found in nature and searching for natural treasures (Table 1). Some nature activities were food-related, such as growing plants, creating miniature indoor gardens, and healthy cooking. While the intervention group received the programme as detailed in the resource kit, the control group received an information folder containing government-recommended physical activity and dietary guidelines for children [27]. To enhance participation, all the sessions were scheduled on weekends. The outcome data was collected using a number of scales and questionnaires addessing eating, active play and nature-related habits before and after the programme, and group session debriefings were held at the beginning and end of the programme. The programme proved popular amongst participants and the results demonstrated significant positive changes on a number of health-related outcomes, such as healthier food habits and an increase in caregiver physical activity levels.

**Table 1 Tab1:** Intervention content and Anticipatory guidance topics, enhanced with connectedness to nature

Session	Activities during the pilot study
1	Welcome and Intro: Setting goals, Communication in the family. Introduce basic concepts regarding parental feeding styles and how these might relate to beliefs about parenting and safety of children. *Connectedness to nature/Outdoor play: active nature games, discovering nature, practicing awareness to sounds, touch, smells, temperature, etc.*
2	Healthy eating: Food groups and reading food labels. How much to eat? Develop parents understanding regarding basic nutrition principles. *Connectedness to nature/Outdoor play: active nature games, discovering nature, practicing awareness to sounds, touch, smells, temperature, etc.*
3	Active play: Methods to encourage active play. Decrease inactive time. Motor skill development for children – the foundation for an active life and safety. Develop of themes/skills regarding: moving for health parents and sedentary behaviours in families. *Connectedness to nature/Outdoor play: active nature games, discovering nature, practicing awareness to sounds, touch, smells, temperature, etc.*
4	Sleeping time: Sleeping friend and sleeping routines. Develop parents understanding regarding sleeping behaviours. *Connectedness to nature/Outdoor play: active nature games, discovering nature, practicing awareness to sounds, touch, smells, temperature, etc.*
5	Fuzzy eating: The outside environment and children. Develop parental skills: how to feed/how to manage food rejection and demands. *Connectedness to nature/Outdoor play: active nature games, discovering nature, practicing awareness to sounds, touch, smells, temperature, etc.*
6	Limit setting: Power struggle. Portion size. Provide parents with understanding about feeding styles and impact on children’s eating. *Connectedness to nature/Outdoor play: active nature games, discovering nature, practicing awareness to sounds, touch, smells, temperature, etc.*
7	Fun with food: Cooking together. To develop understanding about parental modelling of eating, sedentary behaviour and physical activity. *Connectedness to nature/Outdoor play: active nature games, discovering nature, practicing awareness to sounds, touch, smells, temperature, etc.*
8	Encouraging healthy habits: Rules and routines. Throwing, catching, and bouncing skills. Develop skills on providing fail-safe food and activity environments. *Connectedness to nature/Outdoor play: active nature games, discovering nature, practicing awareness to sounds, touch, smells, temperature, etc.*
9	Nature and me: Run & Fun: Promoting PA in Nature. Safety and fun in the nature. Develop parental skills for creating safe outdoor activities in nature environment. *Connectedness to nature/Outdoor play: active nature games, discovering nature, practicing awareness to sounds, touch, smells, temperature, etc.*
10	Farewell and graduation: Summary. *Connectedness to nature/Outdoor play: active nature games, discovering nature, practicing awareness to sounds, touch, smells, temperature, etc.*

### Objectives

The main objective was to test the hypothesis that the proposed healthy lifestyle intervention program Play & Grow, will improve stated outcomes. The effectiveness of Play & Grow intervention, will be tested by conducting a randomised controlled trial (RCT), enhanced with the novel connectedness to nature element, and evaluating immediate and long-term health effects on participating children's active play/sedentary behaviours, zBMI eating habits (Stage 2).To validate the newly created NRS on the preschool population of Hong Kong (Stage 1)To improve general parenting practices (encouragement, positive involvement, problem solving, knowledge of child nutrition and active play, age-appropriate activities and attitudes to nature); and specific parenting practices such as outdoor playtime routines, meal and snack routines, environmental practices and (Connectedness to nature) (Stage 2)To test whether Connectedness to nature encourages healthy lifestyle routines and positively influences healthy eating and active playtime in children aged 2 to 4 in Hong Kong (Stage 2).To test if the key elements of the Play & Grow programme; that is, offering anticipatory guidance [26] and emphasizing parenting skills [23], will be beneficial for the outcomes of the intervention. Further, we assume that the added novel element, Connectedness to nature, will boost the programme and have additional beneficial effects on the children's well-being as a result of increased outdoor time and participation in activities related to nature, active play and food.

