**Discussion:**

A novel measuring tool created specifically for assessing Connectedness to nature, Nature Relatedness Scale (NRS), will be validated and tested for reliability prior to the RCT. The results of the RCT are intended to be used to understand which components of the intervention are most effective. The objectives of this project will be achieved over a 30-month period and will contribute to the research that examines key components of successful healthy lifestyle promotion programmes during early childhood. We predict that the inclusion of Connectedness to nature will significantly improve recognised preschool interventions. Finally, the aim of targeting family involvement will hopefully increase the sustainability of longer-term lifestyle modifications in children.

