
Time spent in nature has also proven to be beneficial for health and wellbeing. The systematic reviews conducted recently have pointed out that nature-related activities enhance general well-being and lead to increased physical activity, a healthier diet, improved sleep and reduced overall stress [15–18]. Worldwide, the most current programmes promoting a healthy lifestyle for children focus almost exclusively on diet and physical activity [19], but few take into consideration a family’s interactions with nature. We suggest that this emerging research area, known as Connectedness to nature or Nature Relatedness [20], is highly related to healthy lifestyle. Unhealthy lifestyle is often explained by environmental factors, while more time spent outdoors in a natural environment is reflected in healthy life patterns [15, 21].

We recently conducted a pilot study in Hong Kong, Play & Grow learning, which is based on the most successful preschool interventions from Sweden and Australia [22, 23]. The results of the pilot work helped formulate the basis of the present project by incorporating the healthy eating and physical activity elements of Play & Grow to which we also included a third novel element; Connectedness to nature. The proposed project will examine this modified Play & Grow intervention aimed at promoting healthy lifestyle in preschool children (aged 2 to 4) through the combined intervention of healthy eating, active play and connectedness to nature habits to children and their families.

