## Methods and design

The objectives of the proposed project will be achieved in two stages over a 30-month period (Fig. 2) in Hong Kong. Firstly, to create a valid measurement tool for the novel Connectedness to nature intervention element, a Nature Relatedness Scale (NRS) will be validated and tested for reliability (Stage 1). To measure the effectiveness of the early-intervention Play & Grow programme, a RCT will be conducted (Stage 2). In order to investigate which particular components of the Play & Grow were most/least effective, the data from the RCT will be used to perform a mediator study at a later stage.

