### STAGE 2. Play & Grow, RCT

In the RCT, the families with 2 to 4 year old children will be randomly allocated to either the intervention group (IG) or waiting-list control group (WLCG). The intervention will comply with CONSORT [34] (Fig. 3). The program is based on the recently completed Play & Grow pilot study, which utilised elements of the three successful healthy lifestyle interventions EarlySTOPP [22], INFANT study [23] and MEND [35], with the addition of the novel Connectedness to nature element.

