#### The novel Connectedness to nature element

The most appropriate way of instilling habits related to nature is to stimulate children's natural curiosity as early in life as possible. This could be done by involving caregivers and educating them about nature-related activities [30, 38–41]. In adults, research demonstrates a correlation between learning about the nature and the length of time spent in nature [42]. Connectedness to nature is described as including basic environmental knowledge, environmental sensitivity and awareness, as well as a commitment to protect nature [28]. In the proposed intervention, we will employ environmental education and nature-related activities to help participating families develop skills conducive to improving playtime and eating habits in children. Examples of the additional elements that make up an 1/3 of the programme are: i) inclusion of active nature games outdoors that involve both children and parents focusing on motor skills, discovering nature, practicing awareness to sounds, touch, smells, temperature, ii) group activities with other families and members, practicing nature related activities, iii) nature homework with follow-ups (collect objects found in nature and make art or grow their own plants), iv) environmental care training (paper waste, water saving, recycling), and v) studying new vegetables and cooking together with them (avocado, using the avocado to make a boat, turning the avocado into guacamole, etc.).

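### The trial randomises only the complete Play & Grow package against a waiting list, so its stated aims about the separate effect of Connectedness to nature and of other components claim more than the design can support

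*Protocol article*

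**What the plan says.** **Design.** Under the Stage 2 heading of the protocol article, families are "randomly allocated to either the intervention group (IG) or waiting-list control group (WLCG"), with no third arm. The Background describes the programme as promoting a healthy lifestyle "through the combined intervention of healthy eating, active play and connectedness to nature habits to children and their families". The Intervention section gives each session three 15-minute parts: guided active play, parent education alongside food play for the children, and outdoor nature games. Table 1 shows a nature activity in all ten sessions. The section on the novel element introduces its list with "Examples of the additional elements that make up an 1/3 of the programme are", which agrees with 15 of 45 minutes. Controls are offered the programme at study completion.

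**Aims at package level.** The main objective and the Stage 2 hypotheses concern Play & Grow as a whole, intervention group against waiting list.

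**Aims at component level.**
- The abstract's Background gives the project aim as finding out whether connecting families to nature improves activity and eating.
- The Objectives include "To test whether Connectedness to nature encourages healthy lifestyle routines and positively influences healthy eating and active playtime in children".
- They also include "To test if the key elements of the Play & Grow programme; that is, offering anticipatory guidance" and parenting skills, are beneficial.
- The abstract's Discussion states: "The results of the RCT are intended to be used to understand which components of the intervention are most effective". It adds: "We predict that the inclusion of Connectedness to nature will significantly improve recognised preschool interventions".

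**Route to component effects.** Methods and design says that "the data from the RCT will be used to perform a mediator study at a later stage", in order to find the most and least effective components.

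**The concern.** A claim about the effect of one component needs a comparison in which that component varies while the others are held fixed. A claim that adding nature improves existing programmes needs a comparator programme without nature. The trial has neither. The stake is interpretation: the closing discussion expects the results to help bring Connectedness to nature into healthy lifestyle recommendations. If the trial is positive, a difference produced wholly or mostly by the play, food or parenting content could be cited in support of a nature-specific recommendation.

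**Working it through.** **1. What the randomised contrast identifies.** Let A be the arm, and let N, E and P mark delivery of the nature, eating/parenting and active-play content. In the intervention arm all three are delivered together, and no arm delivers one without the others. The contrast estimates

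E[Y | A=1] − E[Y | A=0] = β_N + β_E + β_P + any interactions.

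This is one equation with at least three unknowns. Nature's share of the difference could be 0% or 100% with the same arm means, and a larger sample does not change that.

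**2. What the sample size refers to.** The Power and sample size section gives 100 families per group, power 0.8 and α = 0.05. No SD or baseline mean is stated, so the figure cannot be rebuilt from its inputs. Taking α as two-sided (an assumption) and solving backwards:

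d = (1.960 + 0.842) × √(2/100) = 0.396.

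That is the detectable difference for package versus waiting list. No sample size is given for any component.

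**3. What a randomised nature contrast would need (illustration).** Suppose the package effect is d = 0.396 and nature contributes a share f of it. Comparing package with package-without-nature at 80% power needs n per arm = 100/f². Power at 100 per arm is Φ(2.802f − 1.960).

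| Share f | Effect | n per arm | Power at 100 per arm |
|---|---|---|---|
| 1/3 | 0.13 | 900 | 15% |
| 1/2 | 0.20 | 400 | 29% |
| 2/3 | 0.26 | 225 | 46% |

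The shares are assumptions. The table shows only that this question is much larger than the one the trial is sized for.

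**4. Whether the mediator study closes the gap.** Three features of the article count against it.
- Arm is randomised, but the mediator is not.
- The components overlap. The nature element includes motor-skill games and learning about and cooking vegetables, which are also play and food content.
- The mediator and most outcomes are questionnaire measures, and the Participants and randomization section asks that the same caregiver complete them. Correlated reporting is therefore plausible.

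A simulation of 2,000 trials with 100 per arm gave nature no causal effect on the outcome. The package raised the nature score M by 0.5 SD and raised the outcome Y by 0.4 SD through other components. Mediation was declared when both the A→M path and the M→Y path (adjusted for A) had p < 0.05.

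| Residual correlation of M and Y | Nature declared a mediator | Spurious indirect effect | Share of the 0.4 |
|---|---|---|---|
| 0 | 4% | 0 | 0% |
| 0.3 | 93% | 0.5 × 0.3 = 0.15 | 37.5% |
| 0.5 | 95% | 0.5 × 0.5 = 0.25 | 62.5% |

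The indirect effect follows because, with unit residual variances, the coefficient of M given A equals the residual correlation. The documents give none of these inputs. The simulation also has no baseline adjustment, which would remove the part of the correlation that comes from stable differences between caregivers.

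**The case against.** The strongest reply is that the article already separates the two questions: the RCT measures the programme, and a later mediator study examines components. Connectedness to nature is also a measured construct, the Nature Relatedness Scale (NRS), and not only a delivered component. NRS scores can vary within an arm, so the nature objective can be read as a mediation question. Two of the statements are expectations: the abstract predicts a benefit, and the Objectives assume that nature will boost the programme. A package trial against a waiting list is a legitimate first evaluation.

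Much of this stands, and it rules out three stronger readings that a reader might infer.
- *That a positive result would be reported as a nature effect.* The documents do not say so. The main objective and hypotheses are at package level, so misattribution is a risk and not a certainty.
- *That nothing about nature can be learned at any sample size.* This is true only of the randomised component contrast. A mediation effect through the NRS can be estimated, but only under assumptions.
- *That controls receive none of the content.* What they receive while waiting is not stated. Pilot controls were given government activity and diet guidelines. Either way, there is still only one randomised contrast.

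The reply does not remove the mismatch. The Objectives say that the trial will test the nature effect, and the abstract says that the RCT results will identify the most effective components, neither with any qualification. Leaving the mediation methods to a fuller document is acceptable, but no analysis plan can turn a non-randomised mediator into a randomised one.

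**Conclusion.** The point holds as a mismatch between stated aims and design. The package comparison is valid and unaffected. The separate effects of nature, anticipatory guidance and parenting skills have no randomised estimate, and the mediator study can offer exploratory evidence only. This conclusion follows from the two-arm allocation and the joint delivery of the content, and it needs no numerical assumption. The size of the risk in the mediator study does rest on assumptions: false attribution to nature ranged from 4% to 95% as the assumed residual correlation went from 0 to 0.5. The point matters because it changes what the trial may conclude, although it changes nothing about how families are recruited or randomised.

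**What to change.** 1. Reword the abstract aim, the Stage 2 nature objective, the key-elements objective and the abstract's statements on components and added value. Suggested text: *The trial estimates the effect of the complete Play & Grow package, including its nature element, versus waiting list. It does not isolate the effect of the nature element or of any other component.*
2. Limit causal conclusions in the report to that contrast.
3. Label the component question as exploratory mediation, and state that it assumes no unmeasured confounding of mediator and outcome. Take mediators at end of intervention and outcomes at 6 and 12 months, and adjust for baseline mediator and baseline outcome. Table 2 already schedules the NRS and the child eating, activity, sedentary and neophobia measures at all four time points.

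**Cost.** Wording and a modest analysis specification, with no new families, visits or instruments. The downside is a weaker headline claim about nature. If the sponsor wants to keep the causal claim, it would need a randomised arm without the nature element or a factorial design. On the illustration above, that means several hundred families per arm unless nature accounts for most of the package effect.

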## Methods and design

The objectives of the proposed project will be achieved in two stages over a 30-month period (Fig. 2) in Hong Kong. Firstly, to create a valid measurement tool for the novel Connectedness to nature intervention element, a Nature Relatedness Scale (NRS) will be validated and tested for reliability (Stage 1). To measure the effectiveness of the early-intervention Play & Grow programme, a RCT will be conducted (Stage 2). In order to investigate which particular components of the Play & Grow were most/least effective, the data from the RCT will be used to perform a mediator study at a later stage.

**Fig. 2 Fig2:**
[figure not shown]
Tentative project timeline

### STAGE 1. NRS for preschool children – Constructing and evaluating a new measuring instrument

#### Hypothesis

The Nature Relatedness Scale (NRS) for preschool children is a short, reliable, and valid scale for measuring the environmental behaviours of preschool children aged 2–4 years in Hong Kong.

An understanding of children’s nature relatedness becomes more critical as the casual interaction with nature in daily life becomes less obvious. As none of the existing methods for measuring children’s attitudes and behaviours towards environment and nature have been assessed in preschool children, little is known about how they perceive and interact with the natural environment. This baseline is crucial to understanding whether health-promoting interventions targeting Connectedness to nature can be effective. We modified an existing scale for older children in our recent Play & Grow pilot study [32]. Overall, the reliability and construct validity indicated very low applicability to Hong Kong pre-schoolers (Cronbach’s alpha and inter-item correlation of most dimensions, e.g. < 0.50). In the proposed study, we will therefore employ a mixed-method approach, including the above mentioned Play & Grow pilot test (*n* = 39), qualitative interviews with parents (*n* = 10), further modification of the items, and a test of the final short 20-item NRS on children of 2 to 4 years of age (*n* = 100) in 2 different socioeconomic settings in Hong Kong. The qualitative data will lead to construction of an item pool with items representing four theoretical constructs of Nature Relatedness: (1) enjoyment of nature, (2) empathy for nature, (3) sense of responsibility, and (4) awareness of nature. We will collect a sub-sample from 110 children in this age group and explore the factor structure. Participants will be recruited through the Active Health Clinic, HKU. In addition to the Nature Relatedness items, we will include attitude to nature, enjoyment/happiness, psychological health outcomes, and subjective well-being. The Pediatric Quality of Life Inventory 兒科生活品質問卷 (Varni JW, Version 4.0- translated) [33] will be used in the survey to test the criterion validity of NRS for preschool children.

